## Abstract

**Background:**

Very few studies having decision support systems as an intervention report on patient outcomes for cardiovascular disease in the Western world. The potential role of decision support system for the management of blood pressure among Indian hypertensives remains unclear. We propose a cluster randomised trial that aims to test the effectiveness and cost effectiveness of DSS among Indian hypertensive patients.

**Methods:**

The trial design is a cluster randomised community intervention trial, in which the participants would be adult male and female hypertensive patients, in the age group of 35 to 64 years, reporting to the Primary Health Care centres of Mahabubnagar district, Andhra Pradesh, India. The objective of the study is to test the effectiveness and compare the cost effectiveness and cost utility among hypertensive subjects randomized to receive either decision support system or a chart based algorithmic support system in urban and rural areas of a district in the state of Andhra Pradesh, India (baseline versus 12 months follow up). The primary outcome would be a comparison of the systolic blood pressure at 0 and 12 months among hypertensive patients randomized to receive the decision support system or the chart based algorithmic support system. Computer generated randomisation and an investigator and analyser blinded method would be followed. 1600 participants; 800 to each arm; each arm having eight clusters of hundred participants each have been recruited between 01 August 2011 - 01 March 2012. A twelve month follow up will be completed by March 2013 and results are expected by April 2013.

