#### Exclusion criterion

Hypertensive subjects who have been hospitalized within the last 12 months and subjects with a history of cancer (physician certified).

Randomly chosen Primary Health Care centers (PHCs), matched on population size and literacy rate, from a district in the state of Andhra Pradesh, India have been cluster randomized to receive a DSS or a chart based algorithmic support system (Figure 1). The study site, Mahabubnagar district (AP) has four revenue divisions (Wanaparthy, Nagarkurnool, Gadwal and Narayanpet). Demographic details of all the PHCs, stratified by the revenue divisions in Mahabubnagar district, were line listed. The male to female ratio, age group distribution in the PHCs (based on census 2001 data) will be collected from the Andhra Pradesh State Health and Revenue departments. The PHCs will be stratified based on similarity in the study age group demography details (35-64 years of age) and gender distribution. Two PHCs, per intervention arm, will be randomly chosen from each of the four divisions.

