**Figure 1 F1:**
[figure not shown]
Plan for Randomisation.

Physicians from the PHCs, who have been randomised to receive the DSS arm would necessarily be trained and instructed to follow the algorithms and prompts which would arise out of the computer based software, for management of BP. DSS is a software that helps the Physician to (1) undertake a thorough evaluation of risk factors that hypertensive patients may have for developing a cardiovascular disease, (2) to classify the risk level, (3) to follow a software prompted algorithmic guideline based drug management (which would be developed based on Indian Hypertension guidelines II – 2007) and (4) to give alerts on the counselling on lifestyle changes and adherence to medication.

The chart based algorithmic support system will have the guidelines and lifestyle advices printed as a poster format which would then be pasted on the wall of the PHC clinics. The Physicians from the PHCs, who have been randomised to receive the chart based support arm, would be instructed to follow the poster based guidelines for management of BP. The risk factors that need to be specifically elicited, classification of risk among hypertensive subjects, flow chart for drug management and advice for lifestyle interventions would be included as a simple flow chart.

The DSS will be developed, pilot tested in 10% of sample size and then implemented. Physician advice on lifestyle interventions, which would include counselling on reduction of daily salt intake (reduction in papad and pickle intake) and locally relevant fatty food items (ghee, vanaspati and dalda), advice on benefits of brisk walking for 30 min daily (5-7 days in a week), advice on benefits of smoking cessation and adherence to treatment would be available for patients randomized to DSS intervention arm at 0, 6 and 12 months and at 0 month for patients randomized to receive chart based algorithmic support system. Physical measurements such as height, weight, waist circumference, pulse and Blood Pressure (BP) would be measured by a digital BP monitor at 0, 6 and 12 months after study entry (Figure 2).

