### Blood pressure and pulse measurement

All Blood Pressure (BP) measurements taken by the Physician will be performed in a standardised way using digital blood pressure equipments (Model M5, Omron) supplied and validated for the study. BP will be measured on the right upper arm in the sitting position, after a rest of 5 minutes. Using an appropriate sized cuff (which will be recorded) connected to a digital device, and the same arm (which will be recorded), at a similar time of day (which will be recorded), two measurements will be taken at a minute interval. Instructions will be given to the Physicians to ensure that the lower edge of the bladder be placed 2-3 cm above the position of maximal pulsation of the brachial artery in the arm, just above the antecubital fossa. Care would be taken to ensure that the cuff fits firmly, comfortably and is well secured. The mean of the two readings will be used for analysis.

Pulse measurements will be recorded by the digital blood pressure equipment (Model M5, Omron), after a rest of 5 minutes. The digital BP equipment records the systolic, diastolic BP and the pulse in the same sitting, which would be recorded. The average of the two readings will be used for the analysis.

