Randomly chosen 8 PHCs – 4 urban and 4 rural (homogenous in age and gender distribution) for each intervention arm from a district in the State of AP, India would form the study centers. Each PHC has an out patient load of 50-100 patients/day. 2- 4 hypertensive patients are being envisaged to be recruited per day by the Physician per PHC from the patients attending the out patient clinic in the PHC. 10- 20 patients per week per PHC, 20- 40 per month per PHC and 125 patients in 4-6 months. Study recruitment will last from June 2011 to Dec 2011.

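### The Abstract claims investigator blinding, but the physician who uses the allocated tool also recruits, takes consent and measures the primary SBP, so recruitment and outcome measurement are unblinded

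*Protocol article*

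**What the plan says.** The blinding statement is in the Methods paragraph of the Abstract: "Computer generated randomisation and an investigator and analyser blinded method would be followed". The body of the article does not say who the investigator is or how the blinding is kept.

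On allocation, the text under Exclusion criterion says that the PHCs "have been cluster randomized to receive a DSS or a chart based algorithmic support system".

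On delivery, the text after Figure 1 says that physicians in the DSS arm "would necessarily be trained and instructed to follow the algorithms and prompts which would arise out of the computer based software", and that those in the chart arm "would be instructed to follow the poster based guidelines for management of BP".

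On recruitment, the section Sample size, sampling and recruitment says "2- 4 hypertensive patients are being envisaged to be recruited per day by the Physician per PHC". Under Ethical principles, the recruiting physician also obtains the consent signatures.

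On measurement, the section Blood pressure and pulse measurement begins "All Blood Pressure (BP) measurements taken by the Physician will be performed in a standardised way". It prescribes a validated digital device, five minutes' rest, the same arm, recorded cuff size and time of day, and two readings a minute apart whose mean is analysed. SBP at 0 and 12 months is the primary end point, and blood pressure is also an inclusion criterion.

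**The concern.** A reader of the Abstract will take investigator blinding to mean that those who enrol patients or assess the outcome do not know the arm. The body describes one person who uses a visible tool, decides whom to approach, and produces the outcome measurement. Knowledge of the arm could then act in two ways. It could influence which patients are invited, and it could influence how readings are taken, for example through the rest allowed or whether a reading is repeated.

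Both would operate by PHC, hence by arm. A systematic difference between arms of that kind does not shrink as patients are added, so the planned 1600 participants give no protection against it.

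**Working it through.** **Roles set side by side.** No figure in the plan belongs to the blinding claim, so the check is a comparison of sections.

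| Task | Who does it | Where stated | Can this person be unaware of the arm? |
|---|---|---|---|
| Uses software or poster | PHC physician | Text after Figure 1 | No; the tool is the allocation |
| Recruits | PHC physician | Sample size, sampling and recruitment | No |
| Obtains consent | Recruiting physician | Ethical principles | No |
| Measures BP | Physician | Blood pressure and pulse measurement | No |
| Analyses data | Analyst | Abstract | Yes |

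The sentence on measurement could be read as covering only those readings that a physician happens to take. But no other measurer is named, and the cuff-placement instructions are addressed to physicians.

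**Did recruitment follow allocation?** This is indicated but not stated. The PHCs are described as already randomised (Exclusion criterion), physicians are trained according to arm (text after Figure 1), and the 0, 6 and 12 month data are timed from randomisation (Data collection). No section gives the sequence outright.

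**Illustration of what a bias would do.** Inputs from Sample size, sampling and recruitment: SD 19.5 mm Hg, ICC 0.02, coefficient of variation of cluster size CV = 0.25, 8 clusters per arm, 20% loss to follow-up. The cluster size m is 100, or 80 after the loss. The bias sizes are assumptions; the documents give none.

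The plan's own design effects first:
- Equal clusters: 1 + (100 − 1) × 0.02 = 2.98, as stated.
- With CV: DE = 1 + ((1 + CV²) × m − 1) × ICC = 1 + (1.0625 × 100 − 1) × 0.02 = 3.105, which Table 1 gives as 3.1.

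Standard error of the difference in mean SBP, SE = SD × √(2 × DE / n):
- m = 100, n = 800 per arm: 19.5 × √(2 × 3.105 / 800) = 1.718 mm Hg.
- m = 80, n = 640 per arm: DE = 1 + (1.0625 × 80 − 1) × 0.02 = 2.68; 19.5 × √(2 × 2.68 / 640) = 1.785 mm Hg.

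With no true effect and a between-arm bias b, a two-sided 5% t test on 8 + 8 − 2 = 14 degrees of freedom (critical value 2.145) rejects with the noncentral-t probability at noncentrality b / SE:

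| Assumed bias (mm Hg) | m = 80 | m = 100 |
|---|---|---|
| 0.5 | 5.8% | 5.8% |
| 1 | 8.2% | 8.4% |
| 2 | 18.1% | 19.2% |
| 3 | 34.7% | 37.0% |

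A normal approximation gives somewhat higher values (20-21% at 2 mm Hg and 39-42% at 3 mm Hg), so the table is the more cautious version.

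**The case against.** **The investigator may be the central study team.** The article consistently calls the PHC doctor the Physician, never the investigator, and who is masked is detail that an article often leaves to the full protocol. This stands as far as it goes: a literal contradiction is not proven. It does not change the design, because the person who recruits and measures is still unblinded.

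**The measurement is well standardised.** This also stands in part. An automated device with a set rest period and exactly two readings leaves little room for reading or rounding error. The text does not say how extra readings are handled, and the device has no bearing on who is enrolled.

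**Physicians cannot be blinded to such tools.** True. The point does not ask for that; it asks that the protection not be claimed.

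Three stronger readings are tempting and are not supported:
- *That physicians hand-pick a few patients from many eligible ones.* The figure of 2-4 a day is an accrual forecast, not a quota or a selection rule. The article also says "Each PHC has an out patient load of 50-100 patients/day", but applying population prevalence to that load would not give the number eligible: it ignores the age limits, the exclusions, consent and repeat attendance. The extent of physician discretion is unknown.
- *That a bias of 2 or 3 mm Hg is to be expected.* No document figure supports any particular size. At 0.5 or 1 mm Hg the effect on the error rate is small.
- *That readings are likely to be steered around 140/90.* That is an entry threshold, while the primary end point is continuous SBP. A count of readings just under it would be a poor check on either.

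**Conclusion.** The point holds in limited form. The Abstract's statement is wrong if *investigator* includes the PHC physician, and uninformative about the main risk if it does not. On either reading, the article describes unblinded recruitment and unblinded measurement of the primary outcome, with the device and procedure as partial protection. The analyst half of the claim is not in question.

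The conclusion rests on the roles as stated and on the well-supported inference that enrolment followed allocation. If it did not, the recruitment half weakens and the measurement half remains. The size of any bias cannot be derived from the documents. The tabulated error rates show only how sensitive a comparison of 8 with 8 clusters would be. For scale, an assumed 2 mm Hg is half of the 4 mm Hg target in the sample-size text and two fifths of the 5 mm Hg row emphasised in Table 1.

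**What to change.** 1. **Restate the blinding.** Suggested wording: *analyst blinded; the PHC physicians who recruit, treat and measure BP are not blinded*. Carry this limitation into the conclusion when the result is reported.
2. **Protect the remaining 12-month readings.** Record both device readings exactly as displayed, with the time; allow no discretionary repeats; log any that occur. The Abstract places the end of follow-up in March 2013, so on the article's timetable this applies to visits still to come.
3. **Make recruitment checkable.** The Abstract says that all 1600 participants have been recruited, so a new enrolment rule would come too late. Report enrolment counts and baseline characteristics by PHC and arm from the available registers. Adjust the primary SBP comparison for baseline SBP, age and sex, all of which are already collected. Adjustment can reduce the effect of measured imbalance, but it cannot remove selection on unmeasured factors or bias in the 12-month readings, so step 1 is needed regardless.

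The cost is a less favourable blinding statement, minor recording work for staff already in place, and a count from registers.

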**Discussion:**

This cluster randomized community intervention trial on DSS will enable policy makers to find out the effectiveness, cost effectiveness and cost utility of decision support system for management of blood pressure among hypertensive patients in India. Most of the previous studies on decision support system have focused on physician performance, adherence and on preventive care reminders. The uniqueness of the proposed study lies in finding out the effectiveness of a decision support system on patient related outcomes.

**Trial registration:**

CTRI/2012/03/002476, Clinical Trial Registry - India.

## Background

Compared with all other countries, India suffers the highest loss in Potentially Productive Years of Life Lost (PPYLL), due to deaths from cardiovascular disease in people aged 35–64 years (9·2 million PPYLL in 2000, with a projected loss of 17.9 million PPYLL by 2030) [1]. CVD accounted for 29% of deaths and 11% of all Disability Adjusted Life Years (DALYs) in India (all ages, 2005) [2]. Hypertension is directly responsible for 57% of all stroke deaths and 24% of all coronary heart disease deaths in India [3]. The World Health Organization rates hypertension as one of the most important causes of premature death worldwide [4]. The global and regional burden of disease and risk factors study (2001), in a systematic analysis of population health data for attributable deaths and attributable disease burden, has ranked Hypertension in South Asia as second only to child underweight for age [5].

In an analysis of worldwide data for the global burden of hypertension, 20.6% of Indian males and 20.9% of Indian females were suffering from hypertension in 2005 [6]. The rates for hypertension in % are projected to go up to 22.9 and 23.6 for Indian males and females respectively by 2025 [6]. Recent studies from India have shown the prevalence of hypertension to be 25% in urban and 10% in rural subjects in India [3,7-9].

However, only about 25.6% of treated patients had their blood pressure under control, in a multi center study from India on awareness, treatment and adequacy of control of hypertension [10].

Decision support systems have been defined as the tools that help clinicians decide on a course of action in response to an understanding of the patient’s status. These have been devised to improve the management of hypertension and to help the Physician prescribe evidence based standardized medical care that will result in achieving adequate blood pressure control among hypertensive patients. DSS is a software that helps the Physician to (1) undertake a thorough evaluation of risk factors (2) to classify the risk level (3) to follow a software prompted algorithmic guideline based drug management (which has been developed based on Indian Hypertension guidelines II [11] (2007) and (4) to give alerts on the counseling on lifestyle changes and adherence to medication. Mixed results have been shown for DSS in the management of hypertension in the developed world for patient outcomes, but have shown that they improve the Physician performance [12-15]. An improvement in the quality of antihypertensive treatment, concurrently leading to a considerable reduction in drug costs have been shown for DSS [16].

Very few studies having Decision support systems (DSS) as an intervention report on patient outcomes for cardiovascular disease in the Western world. The potential role of DSS for the management of blood pressure among Indian hypertensives remains unclear. We propose a cluster randomised trial that aims to test the effectiveness and cost effectiveness of DSS among Indian hypertensive patients.

### Research question(s)

Are Decision Support Systems effective in lowering the blood pressure (therefore the risk for CVD) and improving the Quality of Life among hypertensive subjects in a Low and Middle Income setting? Are Decision Support Systems (DSS) cost effective in hypertensive subjects for prevention of cardiovascular diseases?

## Methods

### Objective

The objective of the study is to test the effectiveness and compare the cost effectiveness and cost utility among hypertensive subjects randomized to receive DSS or a chart based algorithmic support system in urban and rural areas of a district in the state of Andhra Pradesh, India (baseline versus 12 months follow up).

### Aim

To develop, pilot test and implement a decision support system for hypertensive subjects

1. To recruit and follow up hypertensive subjects for 12 months

2. To evaluate the effectiveness of DSS on CV risk reduction and quality of life scores

3. To compare the CEA and CUA among hypertensive subjects

#### Primary end point

· To compare the SBP (Systolic Blood Pressure) at 0 and 12 months among hypertensive patients randomized to receive the DSS or the chart based algorithmic support system

#### Secondary end point

· To compare the Quality of Life (QoL) scores at 0 and 12 months among hypertensive patients randomized to receive the DSS or the chart based algorithmic support system

· To compare the Cost effectiveness of the DSS versus the chart based algorithmic support system at the end of 12 months among hypertensive patients.

· To compare the Cost utility of the DSS versus the chart based algorithmic support system at the end of 12 months among hypertensive patients.

#### Inclusion criterion

1. Adult male and female Indians in the age group of 35 – 64 years

2. Systolic blood pressure (SBP) of 140 mm Hg or greater and/or diastolic blood pressure (DBP) of 90 mm Hg or greater (irrespective of antihypertensive medications)

3. Informed written Consent form

#### Exclusion criterion

Hypertensive subjects who have been hospitalized within the last 12 months and subjects with a history of cancer (physician certified).

Randomly chosen Primary Health Care centers (PHCs), matched on population size and literacy rate, from a district in the state of Andhra Pradesh, India have been cluster randomized to receive a DSS or a chart based algorithmic support system (Figure 1). The study site, Mahabubnagar district (AP) has four revenue divisions (Wanaparthy, Nagarkurnool, Gadwal and Narayanpet). Demographic details of all the PHCs, stratified by the revenue divisions in Mahabubnagar district, were line listed. The male to female ratio, age group distribution in the PHCs (based on census 2001 data) will be collected from the Andhra Pradesh State Health and Revenue departments. The PHCs will be stratified based on similarity in the study age group demography details (35-64 years of age) and gender distribution. Two PHCs, per intervention arm, will be randomly chosen from each of the four divisions.

**Figure 1 F1:**
[figure not shown]
Plan for Randomisation.

Physicians from the PHCs, who have been randomised to receive the DSS arm would necessarily be trained and instructed to follow the algorithms and prompts which would arise out of the computer based software, for management of BP. DSS is a software that helps the Physician to (1) undertake a thorough evaluation of risk factors that hypertensive patients may have for developing a cardiovascular disease, (2) to classify the risk level, (3) to follow a software prompted algorithmic guideline based drug management (which would be developed based on Indian Hypertension guidelines II – 2007) and (4) to give alerts on the counselling on lifestyle changes and adherence to medication.

The chart based algorithmic support system will have the guidelines and lifestyle advices printed as a poster format which would then be pasted on the wall of the PHC clinics. The Physicians from the PHCs, who have been randomised to receive the chart based support arm, would be instructed to follow the poster based guidelines for management of BP. The risk factors that need to be specifically elicited, classification of risk among hypertensive subjects, flow chart for drug management and advice for lifestyle interventions would be included as a simple flow chart.

The DSS will be developed, pilot tested in 10% of sample size and then implemented. Physician advice on lifestyle interventions, which would include counselling on reduction of daily salt intake (reduction in papad and pickle intake) and locally relevant fatty food items (ghee, vanaspati and dalda), advice on benefits of brisk walking for 30 min daily (5-7 days in a week), advice on benefits of smoking cessation and adherence to treatment would be available for patients randomized to DSS intervention arm at 0, 6 and 12 months and at 0 month for patients randomized to receive chart based algorithmic support system. Physical measurements such as height, weight, waist circumference, pulse and Blood Pressure (BP) would be measured by a digital BP monitor at 0, 6 and 12 months after study entry (Figure 2).

